## Abstract

**Background:**

Rifampicin-resistant tuberculosis (RR-TB) treatment requires combination treatment, which frequently causes serious adverse events and globally results in not much more than 60% treatment success. In Niger, a high cure rate was obtained with a RR-TB treatment strategy based on a second-line injectable drug (SLID)-containing Short Treatment Regimen (STR), with linezolid replacing the SLID in patients with ototoxicity. Given the availability of novel anti-tuberculosis drugs, WHO recommends all-oral RR-TB treatment. Considering the high level of success with the Niger treatment strategy, it would only be justified to replace it in case robust evidence shows that the WHO all-oral bedaquiline/linezolid (BDQ/LZD)-containing STR (experimental arm) performs better than the Niger RR-TB treatment strategy, (control arm) in terms of safety, effectiveness and adherence.

**Methods:**

A pragmatic randomised clinical trial (RCT) using stratified block randomisation, conducted between April 2021 and March 2024, prospectively enrols participants diagnosed with RR-TB in one of the four RR-TB units of the nation. Depending of the month in which patients are diagnosed with RR-TB, patients with FQ-susceptible RR-TB are enrolled in either the experimental arm or control arm.

**Discussion:**

To increase the feasibility of conducting a RCT, embedded in routine activities of all Niger’s RR-TB Units, we used a creative trial design. We randomised by monthly blocks, whereby the regimen used changes every month, using the month of RR-TB diagnosis as stratifying variable. This approach was deemed feasible for Niger's national tuberculosis programme, as it simplifies the work of the clinicians running the RR-TB units. Our creative design may serve as an example for other national programs. Findings will inform national and international RR-TB treatment guidelines, and will also strengthen the evidence-base on how to develop robust RR-TB treatment regimens.

**Trial registration:**

Pan African Clinical Trial Register PACTR202203645724919. Registered on 15 March 2022.

## Administrative information

Note: the numbers in curly brackets in this protocol refer to SPIRIT checklist item numbers. The order of the items has been modified to group similar items (see http://www.equator-network.org/reporting-guidelines/spirit-2013-statement-defining-standard-protocol-items-for-clinical-trials/).

## Introduction

### Background and rationale {6a}

The treatment of rifampicin-resistant tuberculosis (RR-TB), TB resistant to the most powerful anti-TB drug, requires a more complex regimen than the treatment of rifampicin-susceptible TB and more frequently causes severe adverse drug reactions. Until 2016, 18–24 months long and poorly tolerated RR-TB treatment regimens were recommended [1]. These regimens were individualised, thus not standardised, and resulted in not much more than 60% treatment success [2].

In 2016, WHO recommended a standardised short treatment regimen (STR) for patients not yet exposed to second-line drugs and without resistance to the main components of this STR [3]. This STR had achieved a high cure rate (over 80%) among RR-TB patients in multiple programmatic settings [4–8]. However, this STR included a second-line injectable drug (SLID; amikacin, kanamycin or capreomycin), known for causing severe hearing loss as main adverse drug reaction [9]. A review showed that SLID had to be discontinued in about 10% of patients due to adverse events (AE) [10].

The increasing availability of novel drugs, such as bedaquiline (BDQ) and delamanid (DLM), and repurposed drug, such as linezolid (LZD) and clofazimine (CFZ), allow the designing of potent RR-TB treatment regimens solely relying on oral drugs. The 2019 WHO RR-TB treatment guidelines recommend replacing the STR’s SLID with bedaquiline [11]. WHO also recommends research on STR using both BDQ and LZD in patients who have not yet taken second-line drugs for more than one month and for whom fluoroquinolone resistance has been ruled out [12]. This WHO BDQ/LZD-containing all-oral STR resulted in 73% end-of-treatment success in South Africa [13, 14], considerably lower than 83% relapse-free cure obtained with the RR-TB treatment strategy used in Niger [8].

In Niger, patients are treated with a SLID-containing STR. The STR’s SLID is replaced by LZD in patients with contraindications for SLID, mainly ototoxicity. Audiometry is done at baseline and on a monthly basis during treatment. As any audiometry abnormality serves as an indication for switching to LZD, not a single RR-TB patient developed severe hearing loss since 2017 [15]. BDQ is safeguarded for the rare patients with treatment failure or relapse after a first STR, leaving not a single patient without a potentially successful retreatment option [8].

Considering the highly effective RR-TB treatment strategy used in Niger, it was not justified to introduce the WHO BDQ/LZD-containing STR without a rigorous evaluation. We therefore aim to compare the safety, effectiveness and adherence of the WHO all-oral BDQ/LZD-containing STR (experimental arm) with the Niger RR-TB treatment strategy, using a SLID-containing regimen, with LZD replacing the SLID in case of ototoxicity (control arm). To provide high-level evidence on the one hand, but also timely inform local and international guidelines, we used an approach that would be feasible for the local RR-TB programme. We designed a pragmatic randomised clinical trial with stratified block randomisation, using the month of RR-TB diagnosis as stratifying variable. The study protocol is presented here.

### Objectives {7}

The primary objective of the trial is the comparison of safety (any grade 3–5 AE) between the experimental arm (WHO all-oral regimen) and the control arm (Niger RR-TB treatment strategy: a STR with either a SLID or LZD, depending on the presence of audiometry abnormalities).

Secondary objectives include:Describe the effectiveness (“therapeutic success” being defined as “cure” or “treatment completed” without relapse 12 months after the end of treatment) of the two treatment arms, and estimate predictors of effectivenessDetermine adherence to the regimen (assessed by measuring the proportion of patients who took at least 90% of the doses of the RR-TB treatment regimen) of the two treatment arms.

## Methods

We present all items defined by the Standard Protocol Items: Recommendations for Interventional Trials (SPIRIT) statement.

### Trial design {8}

This is a pragmatic randomised clinical trial using stratified block randomisation to compare the safety, effectiveness and adherence of an experimental arm, the WHO all-oral regimen, including BDQ and LZD for all, with the control arm, the Niger RR-TB treatment strategy, using a STR that contains either a SLID or LZD, depending on the presence of audiometry abnormalities. We hypothesise that the STR that contains either a SLID or LZD is more safe, thus superior, than the WHO all-oral regimen, with LZD for all.

### Study setting {9}

Since 2008, RR-TB care in Niger is provided by the National Tuberculosis Programme (NTP), supported by a Belgian NGO, the Damien Foundation (DF), and the Antwerp Institute of Tropical Medicine (ITM).

The country has 20 Xpert MTB/RIF machines (used for molecular RR-TB diagnosis) distributed over its eight Regions. Drug susceptibility testing (DST) for fluoroquinolone and SLID relies on second-line line probe assay (LPA) and culture-based phenotypic DST on solid medium, carried out at the National Referral Laboratory of Niamey (NRL). The NTP applies an exhaustive and systematic quality assurance assessment for all the different types of laboratory tests (sputum smear microscopy, culture and DST). Samples are routinely sent to the ITM in Antwerp for phenotypic and genotypic DST and spoligotyping.

Patients are treated in the country’s four RR-TB units (Niamey, Maradi, Zinder and Tahoua), managed by the NTP, and in close collaboration with DF. RR-TB care is ambulatory, except for bedridden patients who are hospitalised in the referral structures of the four cities. A comprehensive package is provided, including nutritional support, transport costs for patients to reach the RR-TB units, treatment for AE and home visits. Active drug safety monitoring (aDSM) is in place and produces regular reports.

### Eligibility criteria {10}

Patients are eligible for the study if all of the following conditions are met: (1) have bacteriologically confirmed TB with evidence of resistance to rifampicin (for children the diagnosis is not always bacteriologically confirmed as the RR-TB diagnosis may be based on clinical TB diagnosis plus history of a close contact with a confirmed RR-TB case) and susceptibility to fluoroquinolones and (2) be willing and able to give informed consent to participate in the study (signed or witnessed consent if the patient is illiterate; signed or witnessed consent by a child’s parent or legal guardian).

Exclusion criteria: a patient is ineligible for the study if any of the following conditions are present: (1) previous treatment for more than one month with second-line TB drugs included in the treatment regimens to be evaluated (disregard E and Z, which may have been used previously in first-line treatment), (2) a health rate-corrected QT (QTc) interval ≥ 500 msec at baseline that is not corrected by medical management, (3) any other medical contraindications for taking the study regimens, (4) being younger than 6 years old, and (5) diabetes mellitus.

As during routine practice, pregnant women are not excluded from treatment and thus not from the study. The patient information sheet states that there is a lack of safety data during pregnancy.

### Who will take informed consent? {26a}

Patients who are eligible to participate in the study receive information from the RR-TB clinic health staff and have the opportunity to discuss this information. All patients and the legal representatives of minors are asked to provide written informed consent to participate in the study, prior to undergoing any study-specific procedures. Patients are assured that their decision whether or not to participate in the study will not affect the quality of care they will receive. All patients who are ineligible for the study, refuse to be recruited, or withdraw after recruitment, are managed according to national guidelines without negative consequences for them.

### Additional consent provisions for collection and use of participant data and biological specimens {26b}

Patients who agree to participate in the study are asked to sign the consent form. They are informed that their sputum sample will be analysed in Niger and in Belgium and that the leftover of the sputum sample will be stored at the ITM for future research on tuberculosis for at least 10 years. Any future research needs to be approved by relevant Ethics Committees.

## Interventions

### Explanation for the choice of comparators {6b} and intervention description {11a}

The control arm relies on the Niger RR-TB treatment strategy. It relies on the national 9–11- month standard RR-TB STR, which includes moxifloxacin (MFX), CFZ, ethambutol (E), and pyrazinamide (Z) throughout, supplemented by a SLID (amikacin), prothionamide (PTO) and high-dose isoniazid (Hh; 10mg/kg) during the first 4 months (6 months if delayed conversion on smear microscopy at treatment month 4). The SLID is replaced with LZD in case of any hearing disturbance detected on audiometry (4-6 SLID-Hh-PTO-MFX-CFZ-E-Z/5 MFX-CFZ-E-Z, with LZD replacing the SLID in case of any hearing disturbance detected on audiometry, at baseline or during treatment).

In this control arm, the STR uses fluoroquinolone (moxifloxacin) as core drug, with both high bactericidal and sterilising activity. The SLID (or LZD if it replaces SLID) provides early bactericidal activity, and the other drugs add bactericidal or sterilising activity [16].

The experimental arm uses the WHO all-oral regimen, which contains LZD, high-dose isoniazid, prothionamide, high-dose levofloxacin (LFXh), BDQ, CFZ and pyrazinamide for 4 months (6 months if delayed conversion on smear microscopy at treatment month 4), followed by 5 months of treatment with high-dose levofloxacin, BDQ, CFZ and pyrazinamide (4-6 LZD-Hh-PTO-LFXh-BDQ-CFZ-Z/5 LFXh-BDQ-CFZ-Z).

BDQ and fluoroquinolone (levofloxacin) are used as core drugs, thus with high bactericidal and sterilising power. LZD, with good early bactericidal activity, protects BDQ and fluoroquinolone from the acquisition of resistance. The other drugs add bactericidal or sterilising activity [16].

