### Outcomes {12}

Primary endpoint, as a measure of safety: any severe (grade 3–5) AE, with onset of symptoms before the end of treatment, and with the maximum grade measured up to 6 months after the end of treatment.

Secondary endpoints:As a measure of effectiveness: treatment outcome, with relapse-free success (cure or treatment completion without proof of relapse during 12 months of active post-treatment follow-up) as favourable outcome and treatment failure, relapse, lost to follow-up, and death as an unfavourable outcome.As a measure of adherence to the regimen: proportion of daily doses taken.

The definitions used to grade AE are based on French National Agency for Research on AIDS and hepatitis (ANRS) [19].

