### Participant timeline {13}

Depending of the month of RR-TB diagnosis, as shown on the printed Xpert MTB/RIF result, the patient is enrolled on either the control or experimental treatment arm (a coin toss determines which regimen is used for which month). Each patient is treated for 9 to 11 months and is followed actively for 12 months after the end of treatment.

The inclusion assessment includes clinical, bacteriological, laboratory and additional tests described in Table 1.

**Table 1 Tab1:** Enrolment and assessments

		Enrolment	Treatment phase (M = month)											Follow-up		Close-out
			M 1	M 2	M 3	M 4	M 5	M 6	M 7	M 8	M 9	M 10	M 11	MF 6	MF 12	
Eligibility screening		X														
Written informed consent		X														
Allocation		X														
Assessment	Clinical examination	X	X	X	X	X	X	X	X	X	X	X*	X*	X	X	
	Treatment adherence		X	X	X	X	X	X	X	X	X	X*	X*			
	Sputum smear	X (2)	X	X	X	X (2)	X (2)*	X (2)*	X	X	X (2)	X(2)*	X (2)*	X	X	
	Bacteriological culture	X		X		X		X			X	X*	X*	X	X	
	SL-LPA (FQ/Injectables)	X												X±	X±	
	Haemoglobin/CBC#, creatinine@, potassium@, liver enzymes	X	X	X	X	X	X*	X*								
	Visual acuity, test for peripheral neuropathy, Audiometry@	X	X	X	X	X*	X*									
	Chest X-ray	X									X	X*	X*			
	ECG§	X		X		X		X		X		X*	X*			
Safety outcome evaluation													X	X		
Treatment outcome evaluation																X

*If the intensive phase is prolonged

**±** DST carried out at baseline, after reversion (positive culture after conversion) during treatment, and if bacteriological culture is positive during the 12-month post-treatment follow-up (with storage of the baseline, treatment failure or relapse strain for genotypic analysis)

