# To be done if the patient is taking linezolid

@ To be done if the patient is taking a second-line injectable drug

**§** A basic electrocardiogram (ECG) must be performed and additional ECGs done at weeks 1 and 2 after the start of treatment and then once a month during treatment. The ECGs must be repeated if necessary in the event of clinical suspicion of heart rhythm problems and conduction disorders, or other clinical signs (e.g. dehydration and electrolyte disorders)

Abbreviations: *CBC* complete blood count, *ECG* electrocardiogram, *FQ* fluoroquinolone, *M* month, *MF* month of follow-up after treatment completion, *SL-LPA* second-line line probe assay

Baseline sputum samples are systematically sent to the NRL and the ITM in Antwerp. However, as in any life-saving situation, treatment of drug-resistant tuberculosis is not withheld from a patient when DST results are not available. Hence the regimen may be modified once DST results become available {see 11b}.

All patients enrolled in the study undergo regular assessment of clinical and para-clinical parameters as described in Table 1. Monitoring procedures are adapted to fit the drugs used in either the control or experimental treatment arm (e.g. close monitoring of haemoglobin for patients taking LZD; monthly audiometry when a SLID is used).

Before starting treatment with linezolid, providers invite family members to collect blood bags to be able to do a timely blood transfusion in the event of bone marrow aplasia.

Every month sputum samples are collected for bacteriological monitoring using smear microscopy with auramine staining. In case of lack of conversion on smear microscopy at month four (two samples), the intensive phase is extended for one or 2 months maximally.

At month two, four, six and nine (10 or 11 if the intensive phase was prolonged with 1 or 2 months, respectively), samples are collected for culture. Post-treatment follow-up at 6 and 12 months after cure or treatment completion relies on smear microscopy and culture.

In the event of a treatment failure during treatment or relapse during the 12-month post-treatment follow-up, genotyping is done at the ITM in Antwerp on the baseline and failure/relapse sample to determine the strain identify and to distinguish between true treatment failure/relapse and reinfection.

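### The intensive phase for patients without smear conversion at month 4 is given as 6 months in one section and as a one- or two-month extension in another, with no criterion for choosing between one and two

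*Protocol article*

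**What the plan says.** The section on comparators and intervention description {6b, 11a} sets the length of the intensive phase in prose, once for each arm. In the control arm, the injectable (or the linezolid that replaces it), prothionamide and high-dose isoniazid are given "during the first 4 months (6 months if delayed conversion on smear microscopy at treatment month 4"). In the experimental arm, the full combination including linezolid is given "for 4 months (6 months if delayed conversion on smear microscopy at treatment month 4), followed by 5 months of treatment". The regimen shorthand in the same section is "4-6 SLID-Hh-PTO-MFX-CFZ-E-Z/5 MFX-CFZ-E-Z" for control and "4-6 LZD-Hh-PTO-LFXh-BDQ-CFZ-Z/5 LFXh-BDQ-CFZ-Z" for experimental.

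The Participant timeline {13}, in the text below Table 1, returns to the patient whose two smears at month 4 show no conversion. For this patient "the intensive phase is extended for one or 2 months maximally". It then places the end-of-treatment culture, normally at month nine, at "10 or 11 if the intensive phase was prolonged with 1 or 2 months, respectively". The same section gives the overall duration: "Each patient is treated for 9 to 11 months".

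Table 1 has starred paired smears at months 5 and 6 and starred columns at months 10 and 11. The star means only that the intensive phase was prolonged.

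The primary endpoint in Outcomes {12} is "any severe (grade 3–5) AE, with onset of symptoms before the end of treatment".

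**The concern.** Both sections use the same trigger, no smear conversion at month 4, but they attach different results to it. The prose of the intervention description goes from 4 months straight to 6. The timeline allows 5 or 6 and schedules a culture for a 10-month course, which that prose cannot produce.

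The difference concerns the drugs that matter most here. Linezolid and the injectable are given only in the intensive phase. The trial's hypothesis is that linezolid for everyone brings more severe adverse events than a strategy using the injectable or linezolid. The clinicians who apply the extension are not blinded {17a}, and the Discussion itself recognises that clinicians' views of the two regimens can influence their timing decisions. If one unit follows one section and another unit follows the other, the same kind of patient can receive a different length of exposure and be observed for the primary endpoint for a different time.

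**Working it through.** No power or sample-size figure enters this point. The check is a sum of phase lengths, followed by a comparison of the two sections.

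**Inputs**
- Continuation phase: 5 months in both arms ({11a}, prose and shorthand).
- Intensive phase without delayed conversion: 4 months (both sections).
- Intensive phase with delayed conversion: 6 months (prose of {11a}), or 4 + 1 = 5 or 4 + 2 = 6 months (timeline {13}).

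**Formula:** total course = intensive phase + 5 months.

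**The plan's own figure first.** The stated 9 to 11 months is reproduced: 4 + 5 = 9 and 6 + 5 = 11. The range holds under both texts, so it does not separate them.

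**Side by side**

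| Patient | Prose of {11a} | Timeline {13} | Difference |
|---|---|---|---|
| Converted at month 4 | 4 + 5 = 9 | 4 + 5 = 9 | none |
| Not converted, extended by two months | 6 + 5 = 11 | 6 + 5 = 11 | none |
| Not converted, extended by one month | 6 + 5 = 11 | 5 + 5 = 10 | 1 month intensive, 1 month total |

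The texts separate only in the last row. There, linezolid or injectable exposure is 6 against 5 months (6/5 = 1.20, or 20% longer) and the total course is 11 against 10 months (11/10 = 1.10).

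**Effect on the primary analysis.** Onset of an event counts until the end of treatment {12}, and in the Cox model {20a} patients without an event who were cured or completed are censored on that date. For a patient in the last row, time at risk can therefore differ by one month.

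**Does anything else in the article settle it?**
- The 4-6 shorthand can mean 4 or 6, or any of 4, 5 and 6.
- The 9 to 11 months in {11a}, {13} and the outcome definitions {18a} is compatible with totals of 9 and 11 only, or of 9, 10 and 11.
- The starred month-5 smear and month-10 column in Table 1 fit the timeline's scheme, but the table states no rule.
- Trial status dates the last patient's end of treatment nine months after the end of recruitment, so it does not consider an extension at all.

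**What decides between one and two months?** The timeline does not say. A natural inference is that a negative smear at month 5 ends the extension, and the starred month-5 smear is compatible with that, but no section states it.

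**Table 1.** In the text available to me, the row for visual acuity, neuropathy and audiometry ends at month 5, while the row for blood tests runs to month 6. Column positions may have shifted in extraction, so this should be checked against the published table. If it stands, the two safety-test rows imply different lengths for an extended intensive phase.

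**The case against.** The strongest reply is that there is only one rule. The intervention description is an overview, and the timeline is the operational text and the only place where the extension is set out in full. On this view the 6 months is the maximum. The shorthand and the 9-11 month total in the overview section are ranges, Table 1 has paired smears at both months 5 and 6, and a fixed 6 months would leave the month-10 culture without a use. This is a reasonable reading, and it rules out saying that the intervention section as a whole fixes 6 months. It does not remove the discrepancy. The prose gives 6 months twice, without any word marking it as a maximum, and the timeline still lacks a criterion for one month or two.

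The second reply is that the analysis remains defined, and this stands. Censoring uses each patient's actual end of treatment, adherence is read from treatment cards over the actual treatment period, and the 12 months of follow-up start at the actual end. A reader might infer that these quantities become undefined, but they can be computed under either text. Likewise, the secondary model with time-dependent exposure to injectable or linezolid {20a} is built to take varying exposure lengths.

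The third reply is that the rule is worded alike for both arms, and that the Discussion describes standardised care with the same procedures in all units. This also stands as far as it goes: the article contains no evidence that units differ in practice.

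**Conclusion.** The discrepancy is real and lies in current treatment instructions, but it is small. For a patient given a one-month extension, the two sections differ by one month of linezolid or injectable (5 against 6) and one month of total course (10 against 11). All other patients come out the same under both.

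Three stronger readings go beyond the documents:
- **That a patient converting at month 5 necessarily receives a different length under the two sections.** This depends on the unstated assumption that conversion at month 5 leads to a one-month extension.
- **That the arm comparison is biased.** The rule is common to both arms, and no mechanism favouring one of them is shown. Lack of blinding makes uneven application possible, not demonstrated.
- **That a definite number of patients is affected.** The article gives no delayed-conversion rate. If one assumes that 5% to 20% are still smear-positive at month 4, 230 × 0.05 = 11.5 and 230 × 0.20 = 46, so about 12 to 46 patients would meet the trigger. Only those extended by one month fall where the texts differ, so this is a ceiling under an assumed rate and not an estimate.

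What remains is that unblinded units have two written durations for the drugs behind the safety hypothesis, with up to one month's difference in exposure and in time at risk for the primary endpoint. Sample size is not affected. The text should be corrected, mainly because this is easy to do.

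**What to change.** The sponsor should reconcile the intervention description {11a} and the Participant timeline {13} into one extension rule, worded identically for both arms, and state what determines the length of the extension. The month of the final culture and the intensive-phase safety tests in Table 1 (the blood-test row and the row for visual acuity, neuropathy and audiometry) should then be aligned with that rule. Which rule applies is a clinical decision for the sponsor, and this review proposes none.

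The cost is protocol wording. If any of the four units has been working from the other section, a short clarification note is also needed. No change to sample size or to the analysis model follows from it.
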